#### Methods in analysis to handle protocol non-adherence and any statistical methods to handle missing data {20c}

All analyses will be made on the modified intention-to-treat population. For missingness greater than 10% for the co-primary endpoint, multiple imputations by chained equations will be applied as sensitivity analysis with generation of 10 individual data sets.

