**Methods:**

The study is an investigator-initiated, randomized, multicenter, single-blinded, placebo-controlled, clinical trial. Inclusion will continue until one hundred twenty unconscious OHCA patients surviving a minimum of 72 h are randomized. Intervention is a 1:1 randomization to an infusion of methylprednisolone 250 mg following a minimum of 5 min of sustained return of spontaneous circulation in the pre-hospital setting. Methylprednisolone will be given as a bolus infusion of 1 × 250 mg (1 × 4 mL) over a period of 5 min. Patients allocated to placebo will receive 4 mL of isotonic saline (NaCl 0.9%). Main eligibility criteria are OHCA of presumed cardiac cause, age ≥ 18 years, Glasgow Coma Scale ≤ 8, and sustained ROSC for at least 5 min. Co-primary endpoint: Reduction of interleukin-6 and neuron-specific-enolase. Secondary endpoints: Markers of inflammation, brain, cardiac, kidney and liver damage, hemodynamic and hemostatic function, safety, neurological function at follow-up, and mortality. A research biobank is set up with blood samples taken daily during the first 72 h from hospitalization to evaluate primary and secondary endpoints.

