#### Criteria for discontinuing or modifying allocated interventions {11b}

If the next of kin or the trial guardian of a patient refuses or withdraws consent to participate in the study, the patient will be withdrawn from the trial without prejudice to future medical care. Further, if the patient refuses or withdraws consent, when able to, no study observations will be made from the date of request and the patient will be removed from the study.

A patient can be withdrawn from the study by the sponsor-investigator if any of the following occurs: (1) significant intercurrent illness, (2) patient refusal to continue observations, and (3) investigator decides that termination is in the best medical interest of the patient.

If withdrawal of consent occurs, observations will be completed to the date of withdrawal and a final evaluation of the patient’s withdrawal will be made at this point with an explanation for the withdrawal. If withdrawal is due to an adverse event, the patient will be followed until the adverse event is stabilized or resolved.

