### Sample size {14}

The trial is powered at the co-primary endpoint. We chose a priori to power the trial at the “weakest” of the two endpoints, ensuring that we would have sufficient power for both endpoints. As we were not able to find data regarding the effect of methylprednisolone on IL-6- or NSE levels from admission, we chose to power the trial towards a single measurement drawn 48 h after admission. With the assumption that methylprednisolone would reduce IL-6 levels by 20%, the trial would achieve a power of 0.90 at an alpha-level of 0.025 if 112 patients were included. With the assumption that methylprednisolone would reduce NSE levels by 20%, the trial would achieve a power of 0.90 at an alpha-level of 0.025 if 114 patients were included.

Based on the above, inclusion of 120 patients would be sufficient to adjust for missingness due to withdrawn consent, though we estimated from previous studies that approximately 20% of resuscitated OHCA patients would die within 72 h, i.e., before complete assessment of the co-primary endpoint. Further, due to the acute nature of the trial, we expect 10% of post-randomization exclusions and/or patients where consent is not obtained. To achieve a complete set of blood samples from 120 patients, we, therefore, plan to include 1.30 × 120 = 156 patients. We will however stop the trial before if our target at 120 patients is reached.

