### Statistical methods

#### Statistical methods for primary and secondary outcomes {20a}

Analyses of primary and secondary outcomes will be conducted on the intention-to-treat population. Categorical variables will be presented as numbers and continuous variables will be presented as mean (± SD) or median (25th percentile–75th percentile), according to distribution. The primary analyses of the co-primary endpoint will include the modified intention-to-treat population.

Further, we will conduct sensitivity analyses of the co-primary endpoint including all randomized patients. In this analysis, values missing because a patient died prior to blood sampling will be replaced with the median value of the given biomarker in patients dying after blood sampling, but before 30 days.

Continuous endpoints, including the co-primary endpoint, will be assessed at multiple time points and analyzed by application of linear mixed models of covariance. For approximation of normal distribution, logarithmic transformation will be done, as appropriate. The application of linear mixed models will ensure that a higher power is achieved compared to the sample size calculation, which is based on a single measurement (see the “Sample size {14}” section). For analyses of categorical secondary outcomes, chi-squared or Fisher’s exact test will be applied.

Cox proportional hazard models will be applied and sequentially adjusted for the interaction between treatment arm and relevant variables (sex, age, primary ECG rhythm, time to ROSC, pPCI performed, NSE-, and IL-6 levels). Differences in mortality between treatment arms will be depicted in Kaplan–Meier estimate plots and compared with the log-rank test.

R Studio, version 1.2.5001, will be used for all analyses (RStudio Team [2020]. RStudio: Integrated Development for R. RStudio, PBC, Boston, MA; URL: http://www.rstudio.com/).

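### Sections {20a} and {20c} give mortality, neurological outcome and safety two incompatible analysis populations, and the modified set in {20c} must omit some randomized patients

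*Protocol article*

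**What the plan says.** Three statements on analysis populations stand in the current text.

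- Section {20a}, opening sentence: "Analyses of primary and secondary outcomes will be conducted on the intention-to-treat population".
- Section {20a}, same paragraph: "The primary analyses of the co-primary endpoint will include the modified intention-to-treat population".
- Section {20c}, opening sentence: "All analyses will be made on the modified intention-to-treat population".

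Section {20a} then adds that "we will conduct sensitivity analyses of the co-primary endpoint including all randomized patients". In that sensitivity analysis, "values missing because a patient died prior to blood sampling will be replaced with the median value of the given biomarker" seen in patients who died later but within 30 days. This is the only place where the statistical sections refer to all randomized patients.

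Section {12} lists survival, CPC and mRS, and adverse events over the first 7 days, as secondary outcomes. The article does not define the modified set.

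**The concern.** Taken alone, {20a} can be read as a rule with one exception: everything on intention to treat, apart from the primary biomarker analysis. Section {20c} removes that reading, because it sends every analysis to the modified set. Mortality, neurological outcome and safety then have two assigned populations, and the text gives no order of precedence.

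This matters most for these outcomes. A missing biomarker value is a missing-data problem that a model or imputation can address. A death or adverse event in a patient removed from the set is an observed outcome that is not counted. If the removal depends on anything that happens after allocation, the comparison is no longer between the groups as randomized. Unless the choice is fixed before allocation is revealed, either population could be used and either could be defended as following the protocol. Read literally, {20c} also covers the interim look at mortality in section {21b}.

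**Working it through.** **Step 1. Set the statements side by side.**

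| Outcome | {20a} | {20c} |
|---|---|---|
| IL-6 and NSE, primary analysis | ITT by the general sentence, modified ITT by the specific one | modified ITT |
| IL-6 and NSE, sensitivity analysis | all randomized | modified ITT |
| Survival, CPC/mRS, adverse events | ITT | modified ITT |

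The first row can be reconciled, since the specific sentence overrides the general one. The third cannot.

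**Step 2. Do the two sets differ?** If the modified set held everyone randomized, a separate sensitivity analysis of all randomized patients would add no patients. So the modified set omits some of them. The text does not say whom.

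**Step 3. Size at the protocol's own rates.** Section {14} plans 1.30 × 120 = 156 patients, which reproduces. It expects that "approximately 20% of resuscitated OHCA patients would die within 72 h" and allows a further 10% for post-randomization exclusions and/or absent consent.

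- If early deaths are left out (assumption): 0.20 × 156 = 31.2, about 31 patients.
- If only exclusions and missing consents are left out: 0.10 × 156 = 15.6, at most about 16 patients. The article does not split this 10%, and some of these patients cannot be analysed under any rule.
- If both are left out: 0.30 × 156 = 46.8, leaving about 109. If the losses act in sequence, 156 × 0.80 × 0.90 = 112.3 remain.

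The 156 is an upper limit, because {14} allows an earlier stop once the target of 120 is met. The percentages are unaffected.

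**Step 4. What the first case would do to a mortality comparison (illustration only).** Assume 50% mortality at 30 days. The Background gives a figure above 50%, for unconscious patients admitted to intensive care. Then 0.50 × 156 = 78 deaths, of which about 31 (31.2/78 = 40%) fall before 72 h. About 47 deaths remain among about 125 survivors to 72 h (46.8/124.8 = 37.5%).

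Now assume early death of 15% in one arm and 25% in the other, with later mortality of 37.5% in both:

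- All randomized: 0.15 + 0.85 × 0.375 = 46.9% against 0.25 + 0.75 × 0.375 = 53.1%, a difference of 6.25 percentage points.
- Survivors to 72 h only: 37.5% against 37.5%, no difference.

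**The case against.** The strongest reply is that the serious harm depends on a definition the article never gives. A reader might infer that the modified set consists of patients who survived 72 h with complete samples. The abstract does say "Inclusion will continue until one hundred twenty unconscious OHCA patients surviving a minimum of 72 h are randomized", and {14} aims at complete sampling in 120 patients, but both govern when recruitment ends, not who is analysed. Section {20c} itself plans multiple imputation when more than 10% of co-primary values are missing, so a set restricted to complete samples would leave nothing to impute. The median replacement in the all-randomized analysis hints that patients who died before sampling lie outside the modified set, but does not establish it. This objection stands: the 40% loss of deaths is a worst case under assumptions. The Background mortality is also an imperfect input, because the trial excludes primary asystole and expects some patients to wake without needing intensive care.

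Two further readings are tempting and are not supported.

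- Because starting the infusion within 30 min is an inclusion criterion, a reader might infer that patients infused late are dropped from analysis. No section says so.
- Section {11b} states "A patient can be withdrawn from the study by the sponsor-investigator if any of the following occurs: (1) significant intercurrent illness", and a reader might infer that drug-related illness would vanish from the data. The same section follows patients withdrawn for an adverse event until it stabilizes or resolves. Section {18b} keeps consenting patients who discontinue during follow-up in the database, and section {22} reports all serious adverse events as endpoint measures.

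It can also be said that defining a modified set may be left to the full protocol or analysis plan, and that the trial is phase II and calls itself hypothesis-generating for survival. The first is fair, so the missing definition is not the finding. Neither removes the conflict between two statements in the current text.

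**Conclusion.** The contradiction is certain and needs no assumption: survival, CPC/mRS and safety are assigned to ITT in {20a} and to modified ITT in {20c}. That the modified set is smaller than the randomized set follows from how the sensitivity analysis is described. How much smaller is unknown. The range runs from at most about 16 of 156 patients (10%), part of it unavoidable, to about 31 (20%) if early deaths alone are left out, or about 47 (30%) if both groups are. The upper figures assume that early deaths are excluded, which the article does not state.

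The point should be settled before allocation is revealed. Mortality and safety are secondary here, but they will inform the larger trial that the Discussion has in view.

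**What to change.** Replace the opening sentence of {20c}, and align {20a} with it, so that each outcome has one named population:

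- Mortality, CPC/mRS and safety: all randomized patients whose data may legally be used, analysed as allocated, with early deaths kept.
- Co-primary IL-6 and NSE: the modified set is limited to this analysis and uses every available sample, whatever the patient's later survival.
- No randomized patient is excluded from analysis because the infusion was late or missed.

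The 30 min criterion and the withdrawal criteria stay as they are; this is a change to analysis rules only. It costs a few sentences in the protocol and analysis plan and requires no new data.

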#### Plans to give access to the full protocol, participant level-data, and statistical code {31c}

Both protocol and data will be available upon reasonable request and approval from relevant authorities after the trial has been completed.

#### The data monitoring committee {21a}

The DMC will consist of [name] [name], Department of Cardiology, Rigshospitalet and [name], Department of Anesthesiology, Rigshospitalet. Interim analyses and monitoring of overall conduct of the trial will be performed by the DMC and decisions are reported to the sponsor. The DMC is independent of the sponsor and has no competing interests that could impact the trial.

#### Harms: adverse events {22}

AEs will be recorded daily for the first seven days and further entered in a pre-specified form in the eCRF. AEs occurring after day seven will be evaluated at 30- and 180-day follow-up. For each AE, relationship to trial intervention will be rated as “probable,” “possible,” “unlikely,” or “unknown.” Trial investigators will record and evaluate SAEs and SUSARs throughout the trial. If a life-threatening or fatal SUSAR occurs, the Danish Medicine Agency (DMA) will be notified by the sponsor within seven days. Further, the sponsor will inform the DMA on all follow-up action to these SUSARs no more than 8 days after the reporting. Any other SUSARs will be reported to the DMA no later than 15 days from when the sponsor is informed. For assessment of potential causality between the trial intervention, i.e., whether the adverse event is suspected, the summary of product characteristics for Solumedrol will be used. All SAEs occurring at both trial centers will be submitted once a year by the sponsor and a safety report of all trial patients will be submitted to the DMA.

No later than 90 days after the trial has been completed, the sponsor will notify the DMA. If the trial is stopped earlier than planned, the reasons will be reported.

In addition, we will report all SAEs as endpoint measures and all SUSARs in the final trial report and the results of the trial will be reported on EudraCT.

#### Auditing {23}

The DMC will perform interim analyses after 60 patients have participated in the trial and advice the sponsor and the SC thereafter. The DMC will have unlimited access to data upon request. The GCP monitoring will be externally done by the Copenhagen GCP unit and both on- and off-site monitoring will be performed throughout the trial. Monitoring frequency is decided by the GCP unit according to compliance with the trial protocol. The principal investigators will be responsible for all data entered in the eCRF.

#### Plans for protocol amendments (e.g., trial participants, ethical committees) {25}

Relevant protocol revisions and amendments have been communicated and authorized by all relevant authorities. No changes in the current protocol will be done and updates to the clinical trial registry have been done accordingly (https://clinicaltrials.gov/ct2/show/NCT04624776). The trial status will be updated as appropriate.

#### Dissemination plans {31a}

All trial analyses will be done by the SC, and the trial will be unblinded upon acceptance from the committee. Authorship will be granted according to ICMJE guidelines. The main results of the trial will be published in a peer-reviewed international journal regardless of the results and further presented at international congresses. Trial results will be communicated to participating patients and relevant patient relatives if this was requested in the informed consent form.

## Discussion

The aim of this study is to investigate whether an early infusion of 250 mg methylprednisolone can mitigate the systemic inflammatory response seen in comatose patients resuscitated after OHCA. The co-primary endpoints investigated are the biomarkers IL-6, and NSE and we expect to find a reduction of 20% for both biomarkers measured daily from admission to 72 h following admission.

Inflammation has a key role in the complex systemic response, PCAS. Previous findings have shown that circulating levels of inflammatory biomarkers such as IL-6 are associated to outcome following OHCA, i.e., neurological function and death [9, 31]. A possible clinical benefit of early anti-inflammatory treatment in OHCA remains unknown, but several studies targeting inflammation have promising results. Two small studies from 2009 and 2013 found improved survival and neurological outcome following a combination of epinephrine, vasopressin, and glucocorticoid in patients suffering from IHCA [24, 25]. In both of these studies, glucocorticoid intervention was a low dose of 40 mg methylprednisolone injected during CPR and subsequently patients who developed shock were treated with stress-dose hydrocortisone for a maximum of 7 days. Further, a similar recent Danish study in IHCA patients compared the combination of vasopressin and methylprednisolone (40 mg) with placebo administered during CPR and found the combination to be associated with a higher rate of ROSC, but not survival [26]. The most important difference from these studies compared to the present study was the timing (intra-arrest administration) and dosage (40 mg VS 250 mg) of glucocorticoid. The populations studied consisted of IHCA patients, which in a recent observational study has been found to be similar to OHCA patients in demographics, but with a higher burden of cardiovascular comorbidity [32]. Based on current evidence, ILCOR and the European Resuscitation Council do not support the use of glucocorticoids neither as intra-arrest- or post-cardiac arrest treatment in IHCA and OHCA [33, 34]. However, further evidence could clarify the optimal use and possible role of glucocorticoids in cardiac arrest treatment.

Several studies have demonstrated the molecular mechanisms of glucocorticoids, and it is clear that the effects work both through genomic and non-genomic pathways [23, 35], whereas genomic effects alter protein expression within hours, non-genomic effects are believed to kick in within seconds to minutes. A recent review reported rapid non-genomic anti-inflammatory properties both in transformed and immune cells and concluded that these effects are not well understood but could have significant therapeutic value [36]. Further, both genomic and non-genomic effects of glucocorticoids on the cardiovascular system have been suggested to induce an increase in both blood pressure and contractility [37, 38]. Similarly, evidence indicates that glucocorticoids may effectively treat neuroinflammation, which may be comparable to the condition seen in PCAS. Still, the mechanisms are both poorly understood and investigated [39, 40]. As the intervention in this study is a high dose of methylprednisolone injected shortly after ROSC, we hope to achieve essential knowledge about the beneficial non-genomic effects of glucocorticoids by mitigation of the inflammatory part of PCAS at the earliest stage possible and hereby possible improving hemodynamic parameters and neurological stunning. The results of this study should be interpreted as hypothesis-generating in terms of the need to conduct a larger scale study powered towards clinical endpoints such as survival and neurological outcome.

## Trial status

Protocol: v3.1 of September 23, 2021

Recruiting status: First patient included on October 2020. Estimated recruitment completed in July 2022 and completion of 180 day follow up in January 2023.

## Data Availability

Data required to support the protocol are available upon request and approval from relevant authorities.

## Abbreviations

ABG: Arterial blood gas
AE: Adverse event
ALAT: Alanine aminotransferase
ALP: Alkaline phosphatase
AMI: Acute myocardial infarction
ASAT: Aspartate aminotransferase
CCU: Critical care unit
CKMB: Creatine kinase-MB
CPC: Cerebral performance categories
DMA: Danish medicines agency
DMC: Data monitoring committee
ECG: Electrocardiogram
ECRF: Electronic case report file
G-CSF: Granulocyte-colony stimulating factor
GCP: Good clinical practice
GCS: Glasgow coma scale
GDPR: General data protection regulation
GM-CSF: Granulocyte macrophage-colony stimulating factor
HSCRP: High-sensitive C-reactive protein
ICU: Intensive care unit
IFN: Interferon
IHCA: In-hospital cardiac arrest
IL: Interleukin
ILCOR: International liaison committee on resuscitation
INR: International normalized ratio
MCP-1: Monocyte chemoattractant protein-1
MIP-1: Macrophage inflammatory protein-1
MOCA: Montreal cognitive assessment
MRS: Modified Rankin score
NFL: Neurofilament light chain
NSE: Neuron specific enolase
OHCA: Out-of-hospital cardiac arrest
PCAS: Post-cardiac arrest syndrome
PPCI: Primary percutaneous coronary intervention
ROSC: Return of spontaneous circulation
SAE: Serious adverse event
SC: Steering committee
STEMI: ST elevation myocardial infarction
SUSAR: Suspected unexpected adverse reaction
TEG: Thromboelastographic
TNF: Tumor necrosis factor
TNI: Troponin I
TNT: Troponin T
TOR: Termination of resuscitation
TTE: Transthoracic echocardiography
VBG: Venous blood gas
